#### Analyses- primary outcome

The primary analysis will be a modified intention to treat analysis, using the exclusion criteria outlined above. The primary outcome is a binary outcome, so as described above, the number and percentage of intubation attempts where there was successful intubation at the first attempt without physiological instability will be presented separately for the 2 treatment groups. Binary regression (a generalised linear multivariable model, with the primary outcome as the dependent variable, the group allocation as the predictor, and the stratification factors used during randomisation as covariates) will be used to estimate the difference between the treatment groups. The results will be reported as the difference in risk between the 2 treatment groups, with the 95% CI for the risk difference.

#### Primary outcome—sensitivity analyses

As some infants will be randomised more than once, the difference in risk of the primary outcome between the 2 treatment groups, with the 95% CI for the risk difference, adjusted for repeated measures, will also be reported. The model used for this analysis will be a multivariable binary regression as described above, with standard errors estimated allowing for intragroup correlation (using the vce(cluster) option in Stata).

If an imbalance in demographics known to affect intubation success (e.g. postmenstrual age, weight, videolaryngoscope use, operator experience) is detected, a further sensitivity analysis adjusting for the relevant demographics will be conducted for the primary outcome.

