### 10. Randomisation

Each intubation episode is randomly allocated in a 1:1 ratio to either nHF or control, stratified by:
Centre (Royal Women’s Hospital or Monash Newborn),Postmenstrual age (≤ 28 weeks' gestation; > 28 weeks' gestation)Use of premedication for intubation.

The randomisation sequence uses random permuted blocks with varying block sizes. To enable rapid randomisation following the decision to intubate by the clinical team, the randomisation is performed at the cot-side using a smartphone or computer with online access to the Research Electronic Data Capture (REDCap) [4] randomisation tool. Randomisation is web-based, using a password-protected, secure sockets layer (SSL)-encrypted website. The randomisation sequence was developed by an independent statistician at the Murdoch Children’s Research Institute, Melbourne, Australia. The group allocations are unblinded, due to the nature of the intervention. Intubation episodes, rather than infants, are randomised. An infant who has previously had an intubation episode randomised within the study can have subsequent intubation episodes randomised if (1) the premedication randomisation stratum differs between the studied intubations or (2) there is at least 1 week between the studied intubations for intubations where premedications are used.

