## Section 6: Analysis

### 26. Outcome definitions

For all incidence outcomes, incidence is the proportion of first intubation attempts in which that outcome occurred.

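### Infants can be randomised more than once, but only one sensitivity analysis allows for this, and a death or pneumothorax inside two overlapping 72-hour windows is counted twice.

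*SAP article*

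**What the plan says.** Section 10 (Randomisation) sets the unit: "Intubation episodes, rather than infants, are randomised". An infant may re-enter by either of two routes. One is that "the premedication randomisation stratum differs between the studied intubations", for which no interval is stated. The other is that "there is at least 1 week between the studied intubations for intubations where premedications are used".

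In section 27, the primary analysis is "Binary regression (a generalised linear multivariable model, with the primary outcome as the dependent variable, the group allocation as the predictor", with the stratification factors as covariates. It has no term or variance estimate for repeated infants. The sensitivity-analysis paragraph opens "As some infants will be randomised more than once" and adds a second version of the model, "with standard errors estimated allowing for intragroup correlation (using the vce(cluster) option in Stata". The cluster variable is not named, though the infant is clearly meant. Secondary outcomes follow the general model of section 27, which is unclustered, and the subgroup models do not mention clustering either.

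Section 26 says that for every incidence outcome "incidence is the proportion of first intubation attempts in which that outcome occurred". The denominator is thus one per episode, not one per infant. The secondary-outcome list and section 30 (Harms) run the windows for death and pneumothorax to 72 hours from randomisation, so each randomisation opens its own window.

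**The concern.** There are two separate matters.

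First, the SAP acknowledges that observations repeat within infants and has already written the model that allows for it, yet makes the other model the headline. The secondary, safety and subgroup results have no clustered version at all.

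Second, the harms rows have a counting problem that no standard error can repair. An infant intubated without premedication, then re-intubated with premedication within 72 hours, may be randomised twice, with two windows open together. If the infant dies after the second randomisation and inside both windows, the per-episode rule enters one death as two. A reader of the harms table would take the counts as infants who died or had a pneumothorax, and the two columns would no longer be independent.

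**Working it through.** **The plan's own figure.** Section 11 gives 123 episodes per group for 30% v 50%, 90% power and two-sided alpha 0.05. The pooled-variance formula gives n = [1.960·√(2·0.4·0.6) + 1.282·√(0.3·0.7 + 0.5·0.5)]² / 0.20² = 124.0 per group, or 248 in total. Power at 123 per group is 89.8%. The figure reproduces to within one episode per group, and the formula assumes independent episodes.

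**Primary interval.** The number of repeat infants and the within-infant correlation ρ are not in the document. Assume 12, 24 or 48 infants with two episodes each among 246, and ρ from 0.1 to 0.5. With a common variance, a pair of episodes in the same arm adds covariance to the variance of the risk difference, and a pair in opposite arms removes it:

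variance factor = 1 + 2ρ(S − D)/246, where S and D are the numbers of same-arm and opposite-arm pairs.

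- Each episode is allocated separately 1:1, so S − D averages about 0 and the expected factor is about 1.00.
- The 95% range runs from 0.994–1.006 (12 pairs, ρ = 0.1) to 0.945–1.055 (48 pairs, ρ = 0.5).
- If every pair fell in the same arm, the factor would be 1 + 2·0.1·12/246 = 1.01 up to 1 + 2·0.5·48/246 = 1.20, and power at 246 episodes would be 89.5% down to 83.9%. This is a bound, not an expectation.
- In simulated trials of 246 episodes with 20–30% of episodes from infants with two episodes and ρ of 0.3–0.6, the ratio of clustered to independent standard error was about 0.96 to 1.06 (middle 95% of trials).
- In further simulations (24 or 48 pairs, latent correlation 0.5 or 0.9, no covariates), type I error was 5.0–5.4% without clustering and 5.1–5.4% with it. Power was 89–91% either way.

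**Can two windows overlap?** Under the one-week route they cannot, because one week exceeds 72 hours. Under the change-of-stratum route they can, because no gap is stated. An event diagnosed between the two randomisations counts once, since it precedes the second. Only an event after the second randomisation and inside both windows counts twice.

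**What double counting does to the harms comparison.** Let N infants start in each arm with risks r1 and r0. Let a fraction s of all infants be re-randomised within the window, half to each arm, with every event in those infants falling after the second randomisation (the extreme case).

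- Counted in arm 1: N(r1 + s·r1/2 + s·r0/2)
- Counted in arm 0: N(r0 + s·r0/2 + s·r1/2)
- Difference in counts: N(r1 − r0), unchanged
- Episodes per arm: N(1 + s), so the reported risk difference is (r1 − r0)/(1 + s)

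With assumed risks of 8% v 4%, the 4.0-point difference becomes 4.0/1.1 = 3.6, 4.0/1.2 = 3.3 and 4.0/1.3 = 3.1 points if 10%, 20% or 30% of all infants repeat. If 1% do, it is 4.0/1.01 = 3.96.

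**A single shared event (assumed counts, 123 per arm).** Take 4 v 1 events plus one infant whose event lies in both windows, with the two episodes in opposite arms. Six infants are harmed but seven events are reported, 5 v 2, a difference of 3/123 = 2.4 points. Counted once, the result is 5 v 1 (4/123 = 3.3 points) or 4 v 2 (2/123 = 1.6 points), depending on the attribution rule. With rare events, one duplicate is visible in the table.

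**The case against.** The best defence of the primary analysis is that the SAP recognises the problem and commits to reporting the clustered interval as well, so readers will see both. Because episodes are individually randomised, the two should nearly agree. That stands. A reader might infer that the headline interval is invalid or its type I error inflated; the calculations do not support this. The defence does not reach the secondary, safety and subgroup results, for which no clustered version is planned.

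On harms, a reader might infer that double counting pulls the arms together and makes nasal high flow look safer. The documents do not support that either. Same-arm duplicates offset cross-arm ones, so the expected difference in counts is unchanged. The risk difference, which is the measure the SAP reports, shrinks appreciably only if a sizeable share of all infants is re-randomised within 72 hours. The direction would also presuppose which arm carries more harm. In the example, the ratio falls from 4/1 = 4.0 to 5/2 = 2.5, but the SAP does not report ratios.

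It is fair to add that overlap needs a change of stratum within 72 hours and a later event, so it may be rare. It might also be said that attribution belongs in the protocol, which is not shown. However, section 26 of the SAP itself fixes the per-episode rule, and applied as written that rule produces the duplicate.

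**Conclusion.** The point holds in two limited parts. The independence model is primary although the SAP expects repeat infants, and the secondary and safety intervals are never clustered. The numerical effect on the primary result is probably small, in either direction, and unlikely to alter its conclusion. The per-episode counting of 72-hour death and pneumothorax can enter one infant's event twice, in opposite arms about half the time. That misstates the number of infants harmed and makes the harms rows dependent, without on average changing the difference in event counts. All sizes depend on assumed repeat rates, correlations and event risks. The change is worth making because it is cheap and the harms table should count infants correctly.

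**What to change.** - Make the regression with standard errors clustered by infant the primary analysis, naming infant as the cluster variable. Keep the unclustered model as the sensitivity analysis.
- Use the same clustering for all episode-level secondary and safety outcomes.
- For death and pneumothorax within 72 hours, count each infant's event once under one pre-stated attribution rule, for example the most recent preceding randomised episode. Report how many infants had overlapping windows.
- Add a sensitivity analysis restricted to each infant's first randomised episode.
- The one-hour compressions/adrenaline outcome needs no attribution rule, because overlap within one hour is very unlikely.

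No new data are needed: the clustered model is already written, and the additions are a counting rule and one further analysis. There is a small price. Any attribution rule is a convention, and assigning an event to the latest episode may place a late complication of the first episode in the second episode's arm. The first-episode analysis is the check on that.

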#### Primary outcome—subgroup analyses

We will perform pre-specified subgroup analyses for the primary outcome. The prespecified subgroup analyses included in the protocol are:
Postmenstrual age (≤ 28 weeks' gestation; > 28 weeks' gestation)Use of premedication for intubation (yes or no)

In addition, we will perform a pre-specified subgroup analysis for:
3.Operator experience (inexperienced, < 20 previous intubations or experienced, ≥ 20 previous intubations)

This subgroup analysis has been specified following the original trial protocol publication, but prior to submission of this statistical analysis plan or performing any data analysis.

The proceduralists are the clinical staff employed at the two centres:
The Royal Women’s Hospital (13 consultants, 10 fellows, 17 residents, 2 nurse practitionersMonash Newborn (13 consultants, 12 fellows, 13 residents, 4 nurse practitioners)

As the study is not powered for subgroup analysis, these analyses are considered exploratory. Three additional adjusted models will be estimated to explore potential heterogeneity of the effect of the intervention. Each model will include as covariates the stratification factors used in randomisation and an interaction term estimating the interaction between the intervention and the subgroup variable (listed above). Specific subgroup estimates and confidence intervals will be presented obtained from the adjusted model. If there is no evidence of interaction (*p* > 0.05), any differences between subgroups will be regarded as due to chance.

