### 11. Sample size

The sample size of 246 intubation episodes is based on a previous study [5], which examined 206 neonatal intubations by junior medical staff. This study found a 29% successful intubation rate at the first attempt without peripheral oxygen desaturation > 20% or bradycardia < 100 beats per minute. With a power of 90% to detect an increase in the incidence of successful intubation without physiological instability from 30 to 50%, and two-sided alpha 0.05, at least 123 intubation episodes in each group (246 total) are required.

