### 27. Analysis methods

For all outcomes, the difference between the 2 treatment groups will be estimated using multivariable regression, with the outcome as the dependent variable, the group allocation as the predictor, and the stratification factors used during randomisation (gestational age group, premedication use and trial centre) as covariates.

For binary outcome variables, including the primary outcome, the number and percentage of intubation attempts with the outcome will be presented separately for the 2 treatment groups. Binary regression (fitting a generalised linear model) will be used to estimate the difference between the treatment groups. The results will be reported as the difference in risk between the 2 treatment groups, with the 95% CI for the risk difference.

For continuous outcomes, the distribution of each outcome will be assessed visually using graphical methods (histogram and dotplot). If the distribution is considered to be so skewed that the mean is an inappropriate summary measure, the outcome will be summarised using the median, otherwise the outcome will be summarised by the mean.

Where the summary measure is the mean, the mean and SD will be presented separately for the 2 treatment groups. Linear regression will be used to estimate the difference between the treatment groups. The results will be reported as the difference of means between the 2 treatment groups, with the 95% CI for the difference of means.

Where the summary measure is the median, the median and IQR will be presented separately for the 2 treatment groups. Quantile regression will be used to estimate the difference between the treatment groups. The results will be reported as the difference of medians between the 2 treatment groups, with the 95% CI for the difference of medians.

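### The subgroup rule treats an interaction p-value above 0.05 as showing that differences are chance, although the plan says the trial is not powered for subgroup analysis

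*SAP article*

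**What the plan says.** Under the heading on subgroup analyses of the primary outcome (section 27), the SAP names three subgroup variables: postmenstrual age group, premedication use and operator experience (fewer than 20 previous intubations against 20 or more). The third was added after the protocol was published.

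- On power, it says: "As the study is not powered for subgroup analysis, these analyses are considered exploratory".
- On the models, it says: "Each model will include as covariates the stratification factors used in randomisation and an interaction term" for treatment by subgroup. Estimates with confidence intervals for each subgroup will be taken from these models.
- On interpretation, with an interaction p-value above 0.05, "any differences between subgroups will be regarded as due to chance".

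Section 27 gives the general regression model as having group allocation as predictor and "the stratification factors used during randomisation (gestational age group, premedication use and trial centre) as covariates". Operator experience is not among these factors.

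**The concern.** The statement on power and the interpretation rule do not fit together. If the interaction test has little power, a p-value above 0.05 is the expected result even when the treatment effect truly differs between subgroups. The rule does not stop at saying that no difference was shown; it commits the authors to attributing any observed difference to chance. At stake is what the report may say about very preterm infants, intubations with and without premedication, and less experienced operators.

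A second, smaller matter is the list of model terms. Postmenstrual age group and premedication are stratification factors, so their main effects are in the models. Operator experience is not, so on a literal reading it enters the third model only through the interaction. The SAP's own section on sensitivity analyses counts operator experience among the characteristics known to affect intubation success, so its main effect cannot be taken as zero.

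**Working it through.** **The plan's own figure.** Section 11 gives "two-sided alpha 0.05", "With a power of 90% to detect an increase in the incidence of successful intubation without physiological instability from 30 to 50"%, and "at least 123 intubation episodes in each group (246 total) are required". Section 10 gives 1:1 allocation. The pooled two-proportion formula gives 124 per group (248 in total); 123 per group has 89.8% power. The plan's 246 is reproduced to within 2 episodes. No power for an interaction is stated.

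**Power for the interaction.** The interaction is the difference between two risk differences. Its standard error is

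SE = √[ Σ p(1 − p)/n ], summed over the four arm-by-subgroup cells,

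and power for a true interaction of 20 points at two-sided 0.05 is Φ(0.20/SE − 1.96). Twenty points is chosen because it equals the whole effect the trial was designed to detect.

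Assumptions, because the SAP does not supply them: 246 episodes analysed, arms balanced within subgroups, no covariate adjustment, and cell variances from rates of 30% (control) and 50% (nHF).

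With equal subgroups each cell has 61.5 episodes. Then SE = √[2 × (0.21 + 0.25)/61.5] = √0.01496 = 0.122, and power = Φ(1.635 − 1.960) = Φ(−0.325) = 37%.

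| Subgroup split | SE | Power for 20 points | Labelled chance |
|---|---|---|---|
| 50:50 | 0.122 | 37% | 63% |
| 40:60 | 0.125 | 36% | 64% |
| 30:70 | 0.133 | 32% | 68% |
| 20:80 | 0.153 | 26% | 74% |

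Varying the cell rates changes little:

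- A common rate of 40% gives SE = √(0.24 × 4/61.5) = 0.125 and power 36% at 50:50, and 28% at 25:75.
- A benefit of 30 points in one subgroup and 10 in the other (30% to 60%, 30% to 40%) gives 38% at 50:50 and 26% at 20:80.
- A benefit of 20 points in one subgroup and none in the other (30% to 50%, 30% to 30%) gives 39% at 50:50.
- A rate of 50% in every cell, which maximises the variance, gives 35% at 50:50 and 24% at 20:80.

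With equal subgroups and the 30%/50% variances, the interaction detectable with 80% power is (1.96 + 0.84) × 0.122, about 34 points, and the 95% CI half-width is 1.96 × 0.122, about 24 points.

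**The operator-experience model.** Suppose nHF adds 20 points for every operator, experienced operators do 20 points better in both arms, and the split is 50:50. The cells are then control 30% and 50% (mean 40%), and nHF 50% and 70%.

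- With treatment and a numeric treatment-by-experience product but no experience term, the control arm is fitted by its mean of 40%. The estimated effects are 50 − 40 = 10 and 70 − 40 = 30 points, a spurious interaction of 20 points.
- With the experience main effect included, or with the interaction entered as a categorical term covering all four cells, the effects are 50 − 30 = 20 and 70 − 50 = 20 points, and no interaction appears.

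A simulation of the product-only model (246 episodes, 1,000 replicates, no true interaction) rejected in about 19%, 60% and 93% of trials for experience effects of 10, 20 and 30 points. With the main effect included, rejection was about 5% to 6%.

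**The case against.** The strongest reply is that the plan is being cautious. It discloses the lack of power, calls the analyses exploratory and requires an interaction test before any subgroup claim, which is conventional protection against over-reading three underpowered comparisons. It also promises subgroup estimates with confidence intervals whatever the p-value, and Table 2 has rows for all six subgroups with a risk-difference column. This largely stands. A reader might infer that the rule would hide real heterogeneity; the documents do not support that, since the estimates and their imprecision will be on view. What remains is the wording of the conclusion: calling the result inconclusive protects against over-reading just as well, without asserting a null.

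A reader might also infer that the third model will create a false interaction. That does not follow. The sentence listing the model terms does not name group allocation either, so it is probably shorthand for terms added to the main model of section 27. The artefact arises only if a numeric product is fitted without the experience main effect. This is a matter for clarification and not an established defect.

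Finally, the power figures are not properties stated by the plan. They depend on subgroup sizes and rates that it does not give, which is why a range is shown.

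**Conclusion.** The interpretation rule should be changed. Followed as written, it turns a non-significant result from an underpowered test into a conclusion that subgroups do not differ. Under the assumptions above, power for a 20-point interaction is about 26% to 39%, or 24% with the largest possible variance and a 20:80 split, so a true difference of that size would be attributed to chance in roughly 61% to 74% of trials. Equal subgroups are the favourable case. Fewer analysed episodes after post-randomisation exclusions would lower these figures; adjustment for the stratification factors might raise them somewhat.

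The unlisted main effect of operator experience is a minor point of specification. Neither matter touches the primary estimate, its confidence interval or the secondary outcomes, and the subgroup analyses remain exploratory.

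**What to change.** Replace the last sentence of the subgroup paragraph with: *The interaction will be reported as a difference in risk differences with its 95% CI; p > 0.05 will be reported as no clear evidence of heterogeneity (inconclusive), not as absence of heterogeneity.* Show that estimate alongside the subgroup rows in Table 2.

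Extend the model sentence: *Each subgroup model will contain the main effects of treatment and of the subgroup variable as well as their interaction.*

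The cost is two sentences and one table column. No new data and no change to trial conduct are needed.
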